### Outcomes

The primary outcome measure is the 3-month unplanned readmission rate to the AGCH or hospital.

Secondary outcomes measured at 1, 3 and 6 months will include:

Activities of Daily Living (ADL)-functioning, as defined by the Katz-ADL scale.^36^Healthcare utilisation, including institutionalisation in a long-term care facility.Occurrence of delirium and/or falls.HRQOL.^37^All-cause mortality.Satisfaction of the patients and primary caregivers with the provided care.

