### Data collection

Eligible patients and/or legal representatives will be contacted and informed about the study procedures after which written informed consent is obtained. Inclusion and interviewing of patients is conducted by an onsite researcher. Routine data on functioning and risk assessments are collected by a trained registered nurse and physiotherapist as part of the CGA for each patient.^38^
Table 1 gives an overview of measurement of the primary and secondary outcomes over time. These measurements were chosen based on the assessments and data collected from the two historic control groups. The online supplementary table provides an overview of the content and timing of measurements in the AGCH-group compared with the two historic control groups. Measurements during admission are at H1, which is within 48 hours after admission, and H2, which is within 48 hours before discharge. Follow-up is completed by telephone at 1, 3 and 6 months after discharge (P1, P3 and P6).

10.1136/bmjopen-2019-033802.supp2Supplementary data

**Table 1 T1:** Overview of the content and description of the (outcome) measurements and timing of the measurements at the acute geriatric community hospital (AGCH)

	Description and/or instrument	H1	H2	P1	P3	P6
1. Medical and demographical data						
Sociodemographic data	Date of birth, age at admission, sex, level of education, living conditions, marital status	R				
Data on admission	Time spent at the ED, admission diagnosis, date and time of admission	R				
Chronic conditions	Charlson Comorbidity Index^39^	R				
Polypharmacy	Number of drugs	R				
Mortality	Date of death		R	R	R	R
2. Cognitive functioning						
Cognitive impairment	Mini-Mental State Examination^31^	R				
Delirium	Safety management system patient screening (VMS)^42^ Confusion Assessment Method^40^ Delirium Observation Scale^43^	N/D	N/D			
3. Psychosocial functioning and quality of life						
Apathy	Geriatric Depression Scale^44^	N	R	R	R	R
Social network and informal care	Presence and frequency of informal care	R		R	R	R
Quality of life and health status	EQ-5D^37^	R		R	R	R
4. Physical functioning						
Identifying at-risk-patients	ISAR-HP—Identifying Seniors at Risk score^45^	N				
Functional status	Activities of Daily Living (ADL) modified Katz-ADL score^36^	N				
(Im)mobility	Using a walking aid, information from the Katz-ADL questions on exercise	N				
Handgrip strength	Jamar^49^	P				
Gait speed	Short Physical Performance Battery^50^	P				

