### Sample size calculation

In the Hospital-ADL study, 34% of participants experienced a readmission at 90 days.^35^ Assuming that 26% of patients admitted to the AGCH will experience a 90-day readmission, data from 515 patients at the AGCH will yield 80% power to detect an absolute difference of 8% in the readmission rate (which is a 25% reduction in the relative risk) using a two-sided test with an alpha of 0.05.^55^ As we expect 10% loss to follow-up, we aim to include a total of 567 (=515*1.10) patients from the AGCH.

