### Planned statistical analyses

The complete participant flow diagram will show a summary of admissions and study recruitment at the AGCH and will provide study discontinuation rates at 1, 3 and 6-months follow-up.^30^ We will describe the demographic, clinical and prognostic characteristics of the study participants at baseline. The number of participants with missing data will be collected and described alongside our variables to check for the pattern of missingness. Inversely weighted propensity scores will be used to control for any imbalances between the treatment groups.^56^ Propensity scores will be calculated using generalised booted methods. Balance and overlap of propensity score distribution will be assessed. Propensity score weights for the estimation of the average treatment effect will be created using all covariates where groups differed at baseline or that were associated with the 90-day readmission rate. As this is a repeated measures design, we will assume equal weighting for all measurements.^57^

All hypotheses will be tested using a two-tailed significance level of 0.05. All secondary outcomes will be adjusted for multiple testing using a Hochberg method.^58 59^ Descriptive analyses will be performed to examine the participants’ characteristics. Differences in changes over time in outcomes will be compared between groups using multilevel models. All models will include a main effect of treatment group, a linear term for time and an interaction between time and treatment group. Models will be checked with residual and appropriate goodness-of-fit statistics.

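### The stated model tests a difference in slopes, not the 90-day readmission difference the study is sized on, and its straight-line time term can distort curved recovery

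*Protocol article*

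**What the plan says.** The Outcomes section fixes the endpoint: "The primary outcome measure is the 3-month unplanned readmission rate to the AGCH or hospital". The Sample size calculation treats it as a comparison of two proportions at one time: "In the Hospital-ADL study, 34% of participants experienced a readmission at 90 days", then "Assuming that 26% of patients admitted to the AGCH will experience a 90-day readmission", and "data from 515 patients at the AGCH will yield 80% power to detect an absolute difference of 8% in the readmission rate", "using a two-sided test with an alpha of 0.05".

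Planned statistical analyses gives one modelling strategy for the clinical outcomes: group differences in change over time, from multilevel models. It continues: "All models will include a main effect of treatment group, a linear term for time and an interaction between time and treatment group". No contrast at 3 months is named. Models are to be checked with residuals and goodness of fit, but no other form for time is given.

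Study design places assessments at admission, discharge and 1, 3 and 6 months after discharge. The only other models in the article are the cost and QALY regressions under Economic evaluation, which do not address readmission.

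**The concern.** Readmission by 90 days is one yes/no per patient. It has no admission value, so change over time has no natural meaning for it. In a model with group (G), time (t) and their product, the group difference at time t is b_G + b_GT × t. The interaction b_GT is the monthly change in that difference, and b_G is the difference at t = 0. Neither is the difference at 3 months. If the test follows the stated target, change over time, it addresses a different question from the one behind the sample size.

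For outcomes that are repeated, such as Katz-ADL and EQ-5D, a linear term assumes the same monthly change through acute illness, recovery and plateau. An acute-care intervention may well act early and then level off or fade, which a single slope represents poorly.

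**Working it through.** **1. The article's own figure.** Inputs from the Sample size calculation: 34% and 26%, two-sided alpha 0.05, 80% power. With two equal groups and pooled variance (mean proportion 0.30):

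n = [1.96 × √(2 × 0.30 × 0.70) + 0.8416 × √(0.34 × 0.66 + 0.26 × 0.74)]² / 0.08² = (1.270 + 0.543)² / 0.0064 ≈ 514 per group.

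The article gives 515, and power at 515 per group is 80.1%. The figure is therefore a plain comparison of two proportions at 90 days.

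**2. What the stated coefficients test for readmission.** The article gives no readmission times, so constant hazards are assumed: −ln(0.66)/3 = 0.1385 and −ln(0.74)/3 = 0.1004 per month. The cumulative risk at month t is 1 − (1 − p)^(t/3), where p is the 3-month risk.

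| Month | Hospital | AGCH | Risk difference | Log odds ratio |
|---|---|---|---|---|
| 1 | 12.9% | 9.5% | 3.4 points | −0.34 |
| 3 | 34.0% | 26.0% | 8.0 points | −0.38 |
| 6 | 56.4% | 45.2% | 11.2 points | −0.45 |

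On the log-odds scale the groups differ by nearly the same amount throughout, so the slope difference carries little of the effect. In 500 simulated studies of 515 per group, cumulative readmission at 1, 3 and 6 months was fitted by a logistic model with group, linear time, interaction and cluster-robust standard errors. Rejection rates were:

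- direct 3-month comparison: 79%;
- group-by-time interaction: 14%;
- group main effect (time zero): 34%.

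A second run gave 82%, 14% and 37%. The derived contrast b_G + 3 × b_GT reached 87% in that run; it borrows from months 1 and 6 through the linearity assumption.

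The 14% belongs to the log-odds scale. On the absolute-risk scale the difference grows from 3.4 to 11.2 points, so a slope would carry much more signal and most of the power loss would disappear. The slope would still not be the 8-point difference at 90 days.

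**3. Straight line for repeated outcomes.** The article gives no trajectories, so the curves are illustrative. A least-squares line is put through the group difference at months 0, 1, 3 and 6 (mean time 2.5, sum of squares 21).

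- Plateau, 0, 0.5, 0.5, 0.5: slope 1.25/21 = 0.0595; intercept 0.375 − 2.5 × 0.0595 = 0.226. Fitted 3-month difference 0.226 + 0.179 = 0.405 against a true 0.5 (81%), with a baseline difference of 0.23 that does not exist.
- Transient, 0, 0.5, 0.3, 0: slope −0.6/21 = −0.0286; intercept 0.200 + 0.071 = 0.271. Fitted 3-month difference 0.271 − 0.086 = 0.186 against a true 0.3. The slope is negative, but the sign at 3 months is right.
- Months 1, 3 and 6 only: 0.5, 0.5, 0.5 and 0.5, 0.3, 0 both lie exactly on a line (slopes 0 and −0.1). Neither is distorted.

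**The case against.** The strongest reply is that the model sentence follows the one on changes over time, and so may cover only repeated-measures models. It cannot cover literally everything: Table 1 takes satisfaction once, and the cost and QALY regressions have no time term. On that reading the article leaves the primary test unnamed, which an unseen analysis plan could supply. This is a fair reading, but the text does not set the limit, and no other clinical-outcome model is given.

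A reader might infer that the model cannot deliver the primary answer at all. That is too strong. Table 1 records readmission at discharge, 1, 3 and 6 months, and a 3-month contrast can be derived from the fitted model. Nor does the article say that the interaction alone is the readmission test; the 14% applies only if it is used that way.

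A reader might also take three times the slope as the 3-month effect: 0.179 of a true 0.5 (36%), or −0.086 against a true +0.3. Both leave out the group main effect that the model contains. The proper fitted values are 0.405 and +0.186.

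Finally, a reader might infer that patients who die before readmission will be counted as lost or as successes. The article states no rule for deaths, so that is not an error in its text.

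It also stands that the Outcomes section lists secondary outcomes at 1, 3 and 6 months. The article does not say whether the admission value enters as an outcome or as a covariate, and the distortion of the two curves depends on this.

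**Conclusion.** The point holds in a limited form. The article fixes group, linear time and their interaction as the terms of its clinical-outcome models and names no 90-day contrast, while its primary outcome and sample size concern a difference in proportions at 90 days. Neither stated group coefficient is that difference.

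For size, the interaction has about 14% power against about 80% for the direct comparison. This assumes constant hazards, a logistic model on cumulative readmission and 515 per group; it would differ on another scale. For repeated outcomes the 3-month difference is understated by about a fifth (0.405 for 0.5) to nearly two fifths (0.186 for 0.3) in the illustrations. This applies only if recovery is curved and the admission value is modelled as an outcome.

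The documents do not show that the primary question is unanswerable or that the 3-month sign would reverse.

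**What to change.** State the primary analysis as the propensity-weighted difference between groups in the proportion with at least one unplanned readmission within 90 days of discharge, with a confidence interval from robust or bootstrap standard errors. This matches the quantity in the Sample size calculation.

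Limit the multilevel model to the repeated secondary outcomes. Enter visit as a categorical factor with a group-by-visit interaction, name the 3-month contrast as the test, and say whether the admission value is an outcome or a covariate.

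The cost is wording and a few parameters. With visits at 0, 1, 3 and 6 months, three visit terms and three interactions replace one of each, so four are added per secondary model. No new data are needed. Treating death before readmission as a competing event is an optional sensitivity analysis; dates of death are already collected.

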### Economic evaluation

A healthcare and societal perspective is planned for the economic evaluation. The evaluation from the healthcare perspective will only include direct medical costs accrued in the 6 months after the admission to the AGCH. Direct medical costs will only include costs that are funded through the Dutch healthcare system. The evaluation from a societal perspective will include an estimation of the costs of informal care. Costs will be based on the reference prices found in the Dutch Manual for Costing studies and will be set for the final year of data collection (2020 or 2021). According to this guideline, costs will be discounted at 4% and quality adjusted life years (QALY) will be discounted at 1.5%.^60^ Propensity scores will also be used in the economic evaluation. Missing data will be imputed using multiple imputation chained equations, if necessary, for the cost and effect data. We plan to use generalised linear regression models with a gamma distribution and an identity link to account for the right skew of the cost data. A generalised linear regression model will be used to estimate the incremental effect in QALY adjusted for baseline utility estimates with a Gaussian distribution and identify link.^61^ Incremental cost-effectiveness ratios will be calculated using the pooled cost and effect estimates. Bootstrapped cost-effect pairs will be plotted on a cost-effectiveness plane and used to estimate cost-effectiveness acceptability curves.^62^

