**Figure 2 F2:**
[figure not shown]
Diagram of patient participation between February 1st and December 20th, 2019.

**Table 2 T2:** Baseline characteristics of the study participants

Variable	N=212
Age in years, mean (SD)	81.8 (8.4)
Male, N (%)	101 (47.6)
Living arrangements before admission, N (%)	
Independent	172 (81.1)
Assisted living/senior residence	31 (14.6)
Nursing home/other	9 (4.2)
Marital status, N (%)	
Widow/widower	94 (44.5)
Married or living together	71 (33.6)
Single or divorced	46 (21.8)
Education, N (%)	
Primary school	36 (18.7)
Elementary technical/domestic science school	41 (21.2)
Secondary vocational education	65 (33.7)
Higher level high school/third-level education	51 (26.4)
Born in the Netherlands, N (%)	158 (76.0)
Katz-ADL (6-item) score* upon admission, median (IQR)	3.0 (1.0-5.0)
MMSE score†, mean (SD)	23.7 (4.7)
Polypharmacy‡, N (%)	159 (75.0)
Hospitalisation in past 6 months, N (%)	61 (31.1)
Charlson Comorbidity Index§, mean (SD)	2.8 (2.0)
Primary admission diagnosis, N (%)	
Infectious diseases	60 (28.3)
Respiratory (including pneumonia)	54 (25.5)
Gastrointestinal	9 (4.2)
Cardiovascular	20 (9.4)
Neurological	16 (7.5)
Other (eg, falls, delirium, sudden unexplained functional decline)	53 (25.1)

*Score ranging from 0 to 6, with a higher score indicating more dependence in activities of daily living.^36^

†Score ranging from 0 to 30, with a score of ≤23 indicating possible cognitive impairment.^31^

‡Use of five drugs or more.

§Ranging from 0 to 31, with a higher score indicating more severe comorbidity.^39^

ADL, activities of daily living; MMSE, Mini-Mental State Examination.

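### Confounding control rests on the propensity weights alone; adding baseline covariates to the weighted outcome models would protect against imbalance that the weights leave behind

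*Protocol article*

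**What the plan says.** Under Planned statistical analyses, the protocol article gives the task of confounding control to weighting: "Inversely weighted propensity scores will be used to control for any imbalances between the treatment groups". The propensity scores come from boosted models, and the weights target the average treatment effect. They are "created using all covariates where groups differed at baseline or that were associated with the 90-day readmission rate". A check is planned: "Balance and overlap of propensity score distribution will be assessed".

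The outcome models come in the next paragraph. "Differences in changes over time in outcomes will be compared between groups using multilevel models", and "All models will include a main effect of treatment group, a linear term for time and an interaction between time and treatment group". No baseline covariate is named for them. The Economic evaluation section differs here: it uses propensity scores and also plans a model to "estimate the incremental effect in QALY adjusted for baseline utility estimates".

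The endpoint that matters most is under Outcomes: "The primary outcome measure is the 3-month unplanned readmission rate to the AGCH or hospital". The Discussion accepts that baseline differences between the AGCH patients and the historical controls may make the groups hard to match.

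**The concern.** A weighted comparison without covariates is unbiased only as far as the weights balance the groups. If they leave a gap in something that predicts readmission, the gap appears in the group difference. For Katz-ADL or EQ-5D, which have an admission value, the group main effect can absorb a starting difference. Readmission and mortality have no baseline value, so group and time terms cannot do this for them.

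Leftover imbalance is plausible in this study:

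- The controls were recruited in 2010–2014 and 2015–2017; AGCH recruitment began in February 2019.
- Both control cohorts required a stay of at least 48 hours.
- One control cohort excluded patients with severe cognitive impairment and delirium. The AGCH admits patients with delirium, and 29.2% of its first 212 participants were enrolled by proxy consent.

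At stake is a shift of uncertain size in the readmission difference. It could imitate part of the planned effect or hide part of it.

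**Working it through.** **1. The plan's own scale.** Inputs from Sample size calculation: 34% v 26%, two-sided alpha 0.05, power 80%. With equal groups, mean risk 0.30 and difference 0.08:

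n = [1.96·√(2·0.30·0.70) + 0.8416·√(0.34·0.66 + 0.26·0.74)]² / 0.08² = (1.270 + 0.543)² / 0.0064 ≈ 514.

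The stated 515 is reproduced, and power at 515 per group is 80.1%. So 8 points is the yardstick.

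**2. What one unbalanced covariate does.** The documents give no residual imbalance, so this step is an assumption with a range. Let X be standard normal with odds ratio OR per SD. Choose the intercept a so that the mean of expit(a + ln(OR)·X) is 0.34. With a residual standardised difference d, the shift is the mean of expit(a + ln(OR)·(X + d)) minus 0.34.

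| OR per SD | d = 0.1 | d = 0.2 |
|---|---|---|
| 1.2 | 0.4 points | 0.8 points |
| 1.5 | 0.9 points | 1.8 points |
| 2.0 | 1.4 points | 2.9 points |

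Hand check for OR 1.5, d = 0.1: 0.405 × 0.1 × 0.34 × 0.66 = 0.0091, or 0.9 points.

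**3. What such a shift costs.** At 515 per group, a 1-point shift towards the null lowers power from 80% to 68%, and a 2-point shift lowers it to 55%. With no true effect and 34% risk, the standard error is √(2·0.34·0.66/515) = 2.95 points. A 1-point bias then gives 6.3% false positives and a 2-point bias 10.4%.

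**4. Weighting alone against weighting plus covariates.** Simulation with 515 AGCH patients, 1,075 controls (674 + 401), no true effect, and four covariates with log odds ratios of 0.20 to 0.30 per SD, all gaps raising risk in one group. SMD is the standardised mean difference after weighting.

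| Propensity fit | Gap before weighting | Mean absolute SMD | Bias, weights only | Bias, weights + covariates |
|---|---|---|---|---|
| Well fitted, no shrinkage | 0.3 SD | 0.013 | −0.05 points | about 0 |
| Boosted stumps tuned to balance | 0.3–0.4 SD | 0.03–0.04 | 0.6–0.7 points | 0.0 to −0.1 points |
| Strongly shrunken | 0.3 SD | 0.093 | 2.1 points | 0.0 points |
| Strongly shrunken | 0.4 SD | 0.129 | 3.1 points | 0.1 points |

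The spread was the same with and without covariates: an SD of about 2.5 to 2.6 points, for example 2.53 and 2.55 in the 0.3 SD shrunken case. When the shrunken fit was kept but the gaps had mixed directions, the mean absolute SMD was again 0.093 and the bias only −0.3 points.

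**5. Reading the table.** Against 8 points, 0.6 to 0.7 is 8% to 9%, and 2.14 is 27%. In standard errors, 0.7/2.55 = 0.27, which gives a false-positive rate of about 6%; 2.14/2.53 = 0.85 gives about 13%.

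**The case against.** The case for leaving the plan alone is strong in several respects.

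- **The models are not said to contain only these terms.** A reader might infer that covariates are ruled out. The verb is include, and nothing excludes them. The sentence also follows one about change over time, and the model for the 3-month readmission difference is not spelled out, so its application there is inferred. A condensed article may leave the covariate list to the full plan. All of this stands.
- **Strong predictors are not ignored.** A reader might conclude that comorbidity, age or prior admission go unused. Any of them that differs at baseline or is associated with readmission enters the weights, and the weights are the covariate adjustment.
- **The weights are not tuned only to readmission.** Baseline difference is a separate route into the weights and does not depend on the outcome. A confounder of mortality or quality of life has to differ between groups, so that route is aimed at it.
- **The 2-point bias is not a forecast.** It needs both an under-fitted propensity model and gaps that all raise risk in one direction. The 0.4 SD shrunken case would also fail a customary 0.1 balance check. The near-zero bias with covariates is partly expected, because the outcome model there matches the one that generated the data.

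What the objection does not remove is that weighting is the only adjustment named for these models, that the article itself expects baseline differences, and that its QALY model already adds a baseline covariate to the propensity scores.

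**Conclusion.** The point holds as a worthwhile improvement to a sound, standard method. The documents do not support calling it an error, nor claiming that the plan will leave imbalance: no baseline data for the control cohorts are shown.

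Under the simulation assumptions (0.3 to 0.4 SD gaps, all in one direction), the plausible gain with well-tuned boosting is about 0.6 to 0.7 points of the 8-point target. It is about 2 points at 0.3 SD gaps if the propensity fit is strongly shrunken, and nothing if the fit is good. In none of these settings did covariates cost precision.

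The gain has limits. Covariate adjustment does not repair unmeasured changes in hospital practice between 2010 and 2019, nor poor overlap, such as patients with delirium who have no counterpart in one control cohort.

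**What to change.** In Planned statistical analyses, state that every weighted outcome model also includes a prespecified set of baseline covariates recorded in all three cohorts. Examples are age, sex, living situation, Charlson index, number of drugs, hospitalisation in the past 6 months, cognitive status, pre-admission Katz-ADL and admission-diagnosis group.

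For 90-day readmission, fit the weighted logistic model with these covariates, standardise over them, and report the marginal risk difference with a bootstrap confidence interval. That estimate is consistent if either the weight model or the outcome model is right. Where the group-by-time term is the quantity of interest, let the covariates interact with time as well, because main effects alone barely change that term. Report the weighting-only estimate as a sensitivity analysis. Fix the list before outcomes are compared.

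The cost is a few lines of code, with two practical limits:

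- **Availability.** Data collection says the measurements were chosen from those in the control cohorts, so most items should exist in all three. The comparison table is in a supplement that is not shown, so this needs confirming item by item.
- **Gaps.** Incomplete items need imputation or a missing category. In Table 2, "Hospitalisation in past 6 months, N" is 61 (31.1%); 61/0.311 ≈ 196, so about 16 of 212 values are missing. The MMSE is not done in patients who are delirious at inclusion, so cognitive status needs a definition that covers them.
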